## Abstract

**Background:**

Periprosthetic joint infection (PJI) affects approximately 1 % of patients following total hip replacement (THR) and often results in severe physical and emotional suffering. Current surgical treatment options are debridement, antibiotics and implant retention; revision THR; excision of the joint and amputation. Revision surgery can be done as either a one-stage or two-stage operation. Both types of surgery are well-established practice in the NHS and result in similar rates of re-infection, but little is known about the impact of these treatments from the patient’s perspective. The main aim of this randomised controlled trial is to determine whether there is a difference in patient-reported outcome measures 18 months after randomisation for one-stage or two-stage revision surgery.

**Methods/Design:**

INFORM (INFection ORthopaedic Management) is an open, two-arm, multi-centre, randomised, superiority trial. We aim to randomise 148 patients with eligible PJI of the hip from approximately seven secondary care NHS orthopaedic units from across England and Wales. Patients will be randomised via a web-based system to receive either a one-stage revision or a two-stage revision THR. Blinding is not possible due to the nature of the intervention. All patients will be followed up for 18 months.

The primary outcome is the WOMAC Index, which assesses hip pain, function and stiffness, collected by questionnaire at 18 months. Secondary outcomes include the following: cost-effectiveness, complications, re-infection rates, objective hip function assessment and quality of life. A nested qualitative study will explore patients’ and surgeons’ experiences, including their views about trial participation and randomisation.

**Discussion:**

INFORM is the first ever randomised trial to compare two widely accepted surgical interventions for the treatment of PJI: one-stage and two-stage revision THR. The results of the trial will benefit patients in the future as the main focus is on patient-reported outcomes: pain, function and wellbeing in the long term. Patients state that these outcomes are more important than those that are clinically derived (such as re-infection) and have been commonly used in previous non-randomised studies.

Results from the INFORM trial will also benefit clinicians and NHS managers by enabling the comparison of these key interventions in terms of patients’ complication rates, health and social resource use and their overall cost-effectiveness.

**Trial registration:**

Current controlled trials ISRCTN10956306  (registered on 29 January 2015); UKCRN ID 18159.

**Electronic supplementary material:**

The online version of this article (doi:10.1186/s13063-016-1213-8) contains supplementary material, which is available to authorized users.

## Background

Total hip replacement (THR) is a highly successful treatment for painful and damaged joints, with over 80,000 primary THRs carried out in England, Wales and Northern Ireland in 2013 [1]. Periprosthetic joint infection (PJI) is an uncommon but serious complication, affecting approximately 1 % of patients who undergo primary THR and is the indication for over 1,000 revision procedures each year in the National Health Services of England and Wales (NHS) [1, 2].

PJI occurring within 2 years of THR is mainly surgically acquired, and is associated with joint pain and restricted movement. Early infections are commonly caused by virulent bacteria and cause acute onset of pain, effusion, erythema and fever. Delayed infections typically present with symptoms similar to aseptic joint failure including implant loosening and joint pain. If untreated, PJI can result in severe pain, restricted movement, disability and death [3].

Treatment options for hip PJI are the following: surgical removal of devitalised, damaged and infected tissue (debridement) with prosthesis retention and long-term antibiotic treatment; one-stage revision; two-stage revision; excision or amputation. Surgical debridement and retention is considered in early PJI with pathogens susceptible to antibiotics and in patients unfit for revision THR. However, this approach may require lifelong antibiotic treatment [4].

Surgical revision for a hip PJI involves prosthesis removal, debridement, antibiotic treatment and revision THR. The prosthesis is replaced in the same operation (one-stage) or replaced at a delayed interval of between 2 weeks and 12 months (two-stage). In a two-stage revision a temporary ‘spacer’ or temporary joint replacement may be fitted, but the patient has no definitive THR until it is replaced in the second operation. In England, Wales and Northern Ireland in 2013, treatments were one-stage (36 %), two-stage (60 %) and excision (4 %) [1].

The best treatment option is unclear. Two-stage revision has the potential for additional antimicrobial treatment and strategies, but patients’ mobility and quality of life are poor between stages [5, 6]. One-stage revision is becoming increasingly popular because compared with two-stage revision, it has the potential to reduce the overall burden on patients of major surgery, and to reduce healthcare costs [7].

To compare outcomes of one-stage and two-stage revision of infected hip replacements, we systematically reviewed studies that included populations representative of patients in routine clinical practice. Irrespective of the surgical treatment used, the overall 2-year rate of re-infection was 10.1 % (95 % CI 8.2–12.0). In 11 studies with 1225 patients with a hip PJI receiving exclusively one-stage revision, the rate of re-infection at 2 years was 8.6 % (95 % CI 4.5–13.9). After two-stage revision exclusively in 28 studies with 1188 patients, the rate of re-infection at 2 years was 10.2 % (95 % CI 7.7–12.9). We conclude that on the basis of a systematic review of published data, there is no difference in the re-infection rate between one-stage and two-stage revision THR for PJI [8].

### Rationale for the trial

Currently, both one-stage and two-stage revision THRs are carried out for hip PJI. Surgeons from the collaborating centres are in agreement that a proportion of patients could be treated with either one-stage or two-stage revision and that there is no definitive evidence to recommend a specific strategy in terms of clinical or patient outcomes [9].

Unlike previous studies on infection after joint replacement, we plan to use patient-centred outcome measures rather than re-infection rates. This is because patient and public involvement conducted at the lead study centre during the development of this trial protocol, as well as previous research around outcomes after surgery, show that patients are concerned about pain, function and wellbeing after surgery, rather than a single bio-medically defined outcome [10, 11]. This is particularly relevant to PJI as treatment appears to be distressing and has a substantial impact on quality of life [5, 9]. Qualitative research will form an integral part of this trial, informing the design and development of trial processes such as recruitment and randomisation, and to facilitate the interpretation of the trial findings.

#### Null hypothesis

There is no difference in patient-reported outcomes (as measured by the Western Ontario and McMaster Universities Arthritis (WOMAC) Index) at 18 months post randomisation, after one-stage or two-stage revision THR, for PJI.

## Methods/Design

The Infection Orthopaedic Management (INFORM) study is a pragmatic, multi-centre two-armed, parallel group, open, randomised, superiority trial with 1:1 allocation and a nested qualitative study.

The study obtained ethical approval from NRES Committee South West – Frenchay on 31 December 2014 (14/SW/1166).

### Study setting

Patients will be initially recruited from seven NHS secondary care orthopaedic units in England and Wales. If necessary, the trial will be enlarged to more centres to achieve the recruitment target. Selected sites are high-volume tertiary referral centres for infected joint replacements or large NHS orthopaedic units. Participating surgeons at each centre have experience and expertise in both one-stage and two-stage revision treatment.

### Study duration

Recruitment into the trial commenced in March 2015 and 18-month follow-up for all participants is anticipated to be completed by August 2018.

### Participants

Patients will be eligible for the study if they have a hip PJI, and are deemed suitable for either one-stage or two-stage revision surgery by their treating surgeon. The diagnosis of infection, monitoring and decision to proceed to revision surgery, will be determined by the treating surgeon, or multidisciplinary team at the unit. This pragmatic approach should mean that the results of the trial are generalisable to the wider population of patients with this condition.

Patients will provide their written, informed consent to participation before entering the study.

#### Inclusion criteria

 Aged 18 years or above A clinical diagnosis of hip PJIo Diagnosis will be guided by clinical, haematological, biochemical, microbiological and radiological findings from investigations prior to surgery, in accordance with local procedures and at the discretion of the treating clinical team Require revision surgery (either one-stage or two-stage revision THR) for hip PJI in the opinion of the treating consultant orthopaedic surgeon(s)

#### Exclusion criteria

 Unable or unwilling to undergo either one-stage or two-stage revision surgery Lacking capacity to give written informed consent for research

### Interventions

#### One-stage revision THR

One operation: the infected prosthetic joint is removed along with any potentially infected materials, the surgical site is debrided, irrigated and a new THR is implanted under the same anaesthetic.

#### Two-stage revision THR

Two operations: in the first operation, the infected prosthetic joint is removed along with any potentially infected materials and the surgical site is debrided and irrigated. In a second operation, under a separate anaesthetic, a new THR is implanted. The antibiotic regime between stages (e.g. duration, route) will be prescribed according to local guidelines at each centre. The delivery of local antibiotics and the use of a static or articulating spacer will be determined by the treating surgeon depending upon intra-operative findings at the time of the first surgical intervention.

At the time of surgical intervention(s), all cases will have tissue samples collected from five different sites with clean instruments to allow an adequate number and quality of samples to be available for microbiological testing [12].

All other aspects of treatment (e.g. clinical investigations; surgical approach; pre-, peri- and post-operative antibiotic regimens; choice of implants and fixation; analgesia) will be according to the treating surgeon’s normal practice and in line with local policies and procedures.

#### Follow-up

Patients will remain in routine clinical follow-up, with the frequency, duration and clinicians present (e.g. consultant surgeon, microbiologist), determined by local resources and clinical need. Response to treatment will be monitored by blood tests (e.g. C-reactive protein) as clinically indicated and the occurrence of re-infection will be determined by the presenting clinical history and signs as elicited by the treating clinical team, consistent with the preoperative diagnosis of infection.

Research assessments will take place preoperatively (prior to one-stage or first of a two-stage revision), and then every 3 months until 18 months post-randomisation. Outcomes will be assessed using self-report questionnaires, a clinical performance test and extraction of data from medical records (Additional file 1: Figure S1).

#### Safety

Both interventions in the INFORM trial are common surgical procedures for treating hip PJI in the NHS. Surgeons from the centres participating in the trial are experienced in these procedures and specialise in treating PJI. There are no additional risks to patients in taking part in the trial as the clinical interventions and follow-up can be considered standard care. Regular monitoring of outcomes may be perceived as a benefit to some. Patients will be informed of the risks of the operation during the surgical consent process, as is standard practice.

All adverse events will be recorded and serious adverse events will be notified to the appropriate authorities (Research Ethics Committee and Sponsor) within specified timelines.

#### Outcome measures

### Primary outcome measure

The WOMAC Index measured at 18 months post-randomisation.

The WOMAC Index is a validated patient-reported outcome measure, widely used in THR research [13]. The index consists of 24 items (5 pain, 2 stiffness and 17 physical function) divided into three subscales and can be completed in less than 12 minutes. Response options are in a 5-point Likert scale format and the index is validated for completion on site or over the telephone [14].

#### Secondary outcome measures

Complications relating to the study:Complications relating to the study such as hip dislocation, deep vein thrombosis/pulmonary embolism, nerve damage, additional surgery, hospital readmissions, length of stay and re-infection will be collected from hospital medical records and by telephone call or personal visit to participants, every 3 months post-randomisation for 18 months.

#### Post-operative pain

The Brief Pain Inventory short form (BPI-sf) is a validated, widely used, self-administered questionnaire which measures both the intensity of pain (sensory dimension) and interference of pain in the patient’s life (reactive dimension). Patients will complete the eleven questions (four on pain severity, seven on pain interference) rated on a scale of 0–10. Other non-compulsory items have been omitted [15].

#### Hip function

The Oxford Hip Score (OHS) is a short, self-administered questionnaire, which has been validated for use in THR. It consists of 12 questions about activities of daily living directly affected by poor hip function [16].

The 20-metre timed walk test will be used as an objective measure of hip function. This will be performed in hospital preoperatively and at 18 months post randomisation [17].

#### Quality of life and mental wellbeing

The EuroQol EQ-5D-5 L is a validated quality of life measure, consisting a descriptive system (five dimensions; each dimension having five levels) and a visual analogue scale (patient’s self-rated health recorded on a 20-cm scale) [18].

The Hip Dysfunction and Osteoarthritis Outcome Score (HOOS), quality of life subscale consists of four questions each on a 5-point Likert scale with each question being scored from 0 to 4. A normalised score (100 indicating no symptoms and 0 indicating extreme symptoms) is calculated from the subscale. This instrument is specifically designed to capture how the patient’s hip symptoms impact on their lifestyle [19].

The Hospital Anxiety and Depression Scale (HADS) is a validated self-reported measure used to detect anxiety and depression in people with physical health problems. The HADS comprises two subscales, depression and anxiety. Each subscale has a score ranging from 0 to 21. Items are rated on a 4-point Likert-type scale ranging from 0 to 3, generating a scale range of 0 to 42 points, with higher scores representing greater symptom severity [20].

#### Cost-effectiveness

All health service resource use relating to the hip PJI will be collected from hospital records and from patient self-completed questionnaires. This will include the interventions, additional inpatient stays, outpatient appointments and any related surgical or non-surgical procedures. Questionnaires will collect information on non-treating hospital resource use, community health and social service use, travel costs, time off work and informal care. Resource use logs, to act as an aide memoire, will be given to patients at their initial preoperative assessment to help them complete the follow-up questionnaires.

### Sample size

The required sample size has been set at 128 participants; allowing for a 13 % loss to follow-up at 18 months post randomisation, a total of 148 patients will need to be recruited. To reach this target, we will need to identify 290 eligible patients: the recruitment rate observed in a surgical trial involving THR recently conducted in the coordinating centre was 51 % with an attrition rate of 13 % [21].

A sample size of 128 patients will provide 80 % power to test that one surgical approach is superior to the other approach 18 months post randomisation by 10 points on the WOMAC Index, equivalent to a 0.5 standard deviation difference. The significance level for this superiority hypothesis is set at 5 % (two-sided).

Although it is known that infection following total joint replacement reduces patient satisfaction and seriously impairs functional health and quality of life, there is no published research on the likely difference in patient-reported outcomes between patients undergoing one-stage and two-stage revision for PJI. The standard deviations observed prior to one-stage or two-stage revision surgery for WOMAC global and sub-indices range between 18 and 25 [22, 23].

### Randomisation

After patients have been consented to the trial and have agreed to be randomised, preoperative outcome measures will be collected. They will then be randomly allocated to one of the two treatment groups (one-stage or two-stage revision surgery) in a 1:1 ratio. Randomisation within blocks of varying size will be conducted separately for each hospital. Block sizes will not be disclosed.

Randomisation will take place as close as possible to the time of surgery (maximum 12 weeks prior to surgery), whilst allowing sufficient time to plan the operation and order necessary equipment.

The randomisation sequence will be generated centrally by computer, and administered via the Internet by the Bristol Randomised Trial Collaboration.

### Blinding

Due to the nature of the interventions, it is not possible to blind patients or staff to allocation. Patients will be informed of the allocated surgery after they have completed the preoperative assessments.

### Statistical analysis

Analysis and presentation of data will be in accordance with the Consolidated Standards of Reporting Trials (CONSORT) guidelines for reporting randomised trials, and the final report will also follow the CONSORT extension for non-pharmacological interventions (see Additional file 1: Figure S1 – study flowchart). The baseline characteristics and primary outcomes will be described by treatment group. The secondary outcomes will also be presented by treatment group and where required by assessment point. Means with standard deviation or median with inter-quartile range will be reported for continuous variable, frequency and proportions for categorical or binary variables, as appropriate.

The primary outcome is the continuous WOMAC Index collected at 18 months postrandomisation. The primary analysis will consist of a generalised linear mixed model (GLLM) with identity link function regressing baseline and 18-month WOMAC measures on the treatment indicator (one-stage treatment versus two-stage treatment), measurement point (baseline versus 18-months) and their interaction (treatment × measurement point). This will be a two-level hierarchical GLLM (measurements within patients). As the treatment allocation is stratified by hospitals and participants are nested within a small number of hospitals, the primary analysis will also be adjusted for indicators of hospital centre introduced as fixed effects (using the coordination centre as a reference). The intervention effect will be assessed using appropriate contrast to identify the mean difference in WOMAC at 18 months and due emphasis will be put on the associated 95 % confidence interval and the *p* value resulting from the Wald-test associated with this contrast. The primary analysis will be based on the intention-to-treat principle, analysing participants in the groups to which they were randomised. All individuals with a WOMAC Index observed at baseline and/or at 18 months will be considered for this analysis. The GLLM with identity link function is based on a likelihood method, which provides unbiased estimation under the missing at random hypothesis despite the presence of missing outcome information. Various sensitivity analyses will be conducted to adjust for imbalance baseline characteristics between treatment groups, assess the clustering at surgeon level or investigate the impact of missing data using various imputation strategies. Finally a per-protocol analysis will be conducted.

Secondary analyses will firstly analyse all repeated measurements of WOMAC to compare the trajectory of recovery/change between treatment groups. Similarly to the analyses of the WOMAC Index, we will firstly investigate the differences in OHS, HADS and 20-metre timed walk test between treatment groups at 18 months post randomisation (using a time × treatment group interaction and appropriate contrast). We will then analyse all repeated measurements of those secondary outcomes to compare the trajectory of recovery/change between treatment groups. GLLMs with appropriate link function will be used (using, according to the nature of the outcomes, linear, logistic or Poisson two- or three-levels mixed regression) to assess the difference between treatments in secondary outcomes and take into account data clustering. Length of hospital stay will be assessed and compared using generalised linear (Poisson or negative-binomial) or survival analysis model. The trial is not primarily powered for these analyses and the results will be interpreted with due caution.

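### The primary model uses only baseline and 18-month WOMAC, so patients lost before 18 months enter through the preoperative score alone although interim WOMAC is collected

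*Protocol article*

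**What the plan says.** In the protocol article, the section Statistical analysis defines the endpoint: "The primary outcome is the continuous WOMAC Index collected at 18 months postrandomisation". The primary analysis is a mixed model "regressing baseline and 18-month WOMAC measures on the treatment indicator", with measurement point at two levels, the treatment-by-time interaction, and hospital as a fixed effect. On who is included it says "All individuals with a WOMAC Index observed at baseline and/or at 18 months will be considered for this analysis". It justifies the likelihood method because it "provides unbiased estimation under the missing at random hypothesis despite the presence of missing outcome information". Sensitivity analyses will, among other things, "investigate the impact of missing data using various imputation strategies".

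The section Follow-up places research assessments before surgery "and then every 3 months until 18 months post-randomisation". The secondary analyses begin: "Secondary analyses will firstly analyse all repeated measurements of WOMAC to compare the trajectory of recovery/change between treatment groups". Interim WOMAC scores therefore exist. That they are taken at every 3-month assessment is an inference from these two sections, because the figure with the visit schedule is not shown.

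**The concern.** Missing at random is always relative to the data in the model. In the two-occasion likelihood, the only WOMAC value available for a patient without an 18-month score is the preoperative one. Loss is then ignorable only if, given arm, centre and preoperative WOMAC, it is unrelated to 18-month WOMAC. A patient who stops returning questionnaires after a poor recovery that the trial has itself recorded breaks this condition. Put the recorded visits in the model and the same loss becomes ignorable.

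This trial gives some reason to expect such loss. The Background says that mobility and quality of life are poor between the stages of a two-stage revision, so the arms are expected to differ in interim course. They also differ in the number of operations, and the trial is open. The sample size section plans for 13% loss. At stake is a possible bias in the primary contrast that data already in hand could remove.

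**Working it through.** **Inputs from the protocol article (Sample size, Randomisation).** Target 10 points = 0.5 SD, so SD 20; two-sided 5%; 80% power; 1:1 allocation; 128 evaluable; 13% loss; 148 recruited.

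**The plan's own figure.** The normal approximation gives 2 × (1.960 + 0.842)² × 20²/10² = 62.8, so 63 per arm (126). The t-test calculation gives 63.8, so 64 per arm = 128. Then 128/0.87 = 147.1, so 148. The stated figures reproduce. Expected loss is 0.13 × 148, about 19 patients.

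**Assumptions not in the documents.** Correlation of baseline with later WOMAC 0.4; the correlation between post-operative visits; and how loss depends on interim WOMAC. These are varied below.

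**Precision when loss is unrelated to WOMAC.** Relative to complete data, the variance is (1 − R²m)/(1 − m), where m = 0.13 and R² is the share of 18-month variance explained by what was observed before loss.
- Baseline only, R² = 0.4² = 0.16: (1 − 0.0208)/0.87 = 1.126.
- With interim visits, R² = 0.60: 0.922/0.87 = 1.060.
- With interim visits, R² = 0.77: 0.8999/0.87 = 1.034.

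In standard-error terms the two-occasion model is worse by √(1.126/1.060) = 1.03 to √(1.126/1.034) = 1.04. Simulated trials of 148 patients at 13% loss gave 2–5% when loss was unrelated to WOMAC and practically no difference when it depended on interim WOMAC.

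**Bias, first set.** Large simulated samples; arms with the same recovery course; post-operative correlation decaying with each further visit; all loss after month 12; log-odds of loss rising by the stated slope per SD of worse 12-month WOMAC. Overall loss is 13% in every row.

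| Loss by arm | Slope | Adjacent correlation | Two-occasion bias (points) |
|---|---|---|---|
| 8% / 18% | 1 | 0.88 | 1.0–1.1 |
| 8% / 18% | 1 | 0.85 | 1.0 |
| 8% / 18% | 1 | 0.70 | 0.6 |
| 8% / 18% | 0.5 | 0.88 | 0.6 |
| 8% / 18% | 0.25 | 0.88 | 0.3 |
| 11% / 15% | 1 | 0.88 | 0.4 |
| 11% / 15% | 1 | 0.70 | 0.2 |
| 5% / 21% | 1 | 0.88 | 1.6–1.7 |
| 5% / 21% | 1 | 0.70 | 0.9 |
| 13% / 13% | 1 in one arm, 0 in the other | 0.88 | 1.4 |
| 13% / 13% | 1 in both | 0.88 | about 0 |

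The all-visit model stays within about 0.05 points of the full-data result. That is expected, because the assumed loss depends only on a value the model contains. The last two rows show that equal loss rates protect the contrast only if the mechanism, and likewise the recovery course, is also the same in both arms.

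**Bias, second set.** 148 patients; loss possible after each visit from month 3 to month 15; log-odds changing by 0.06 per point (1.2 per SD) of the latest score; arms recovering at different speeds; adjacent correlation 0.70 or 0.85.
- Same mechanism in both arms: 0.9–1.1 points at 13% loss and 1.3–1.9 at 25%. The all-visit model is within 0.1.
- Opposite mechanisms by arm (an extreme case): 2.8–3.7 points at 13% and 5.3–7.1 at 25%. The all-visit model is within 0.2.

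**Scale.** With 148 complete patients the standard error is 20 × √(2/74) = 3.29. With 13% loss in the two-occasion model it is 3.29 × √1.126 = 3.49. A bias of 1.0 point is 0.29 of a standard error, and 1.7 points is 0.49.

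**The case against.** Using baseline and the final assessment for an endpoint defined at one time is a legitimate choice. The likelihood method keeps patients with only one of the two values. The unbiasedness statement is conditional on missing at random and true as written. Interim WOMAC is analysed in the first secondary analysis, and imputation sensitivity analyses are planned that may well use it; whether they do is a matter for the analysis plan, which is not shown. The bias depends on loss rates by arm, slopes and correlations that the documents do not give, and milder assumptions bring it to a few tenths of a point. An all-visit model does not help patients lost before any post-operative questionnaire, nor does it remove bias from events after the last visit.

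All of this stands, and it limits what can be claimed. A reader might infer that the trial throws its interim data away, that the primary estimate is biased, or that the protocol contradicts itself. The documents support none of these: the interim data are used elsewhere, bias arises only under particular loss mechanisms, and no two statements conflict. A reader might also expect a large gain in power, but at 13% loss the gain is slight.

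The objection does not remove the point that the primary confidence interval and p value come from the two-occasion model, whatever the secondary and sensitivity analyses show.

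**Conclusion.** The point holds as a cheap improvement. As fixed in the article, the primary model relies on a stronger missing-at-random condition than the collected data require. At 13% overall loss and SD 20, the possible bias is roughly 0.2 to 1.7 points over the main scenarios, or 2–17% of the 10-point target. It is zero if loss depends only on baseline, arm and centre, and reaches about 3 to 4 points only if the loss mechanisms run in opposite directions in the two arms. A flatter decay of the post-operative correlations would raise the main-scenario figures somewhat. All of these figures rest on assumed correlations, recovery courses and loss mechanisms, and on WOMAC being collected at the 3-monthly assessments. The precision gain is 0 to 5% of the standard error. The planned 128 and 148 are unaffected.

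**What to change.** Fit the primary mixed model to all scheduled WOMAC assessments: time as categories by treatment, centre as a fixed effect, and an unstructured within-patient covariance. Name a fallback covariance structure in case of non-convergence, and check whether the covariance differs by arm, since the between-stage period may alter it. Keep the 18-month arm difference as the primary contrast and the two-occasion model as a sensitivity analysis. If the primary model is to stay as it is, state at least that the planned imputation models will include interim WOMAC.

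The cost is a change of wording, made before the outcome data are analysed. No new data are needed, and neither the estimand nor the sample size changes. The downside is more covariance parameters to estimate from 148 patients, with a possible need for the fallback structure.
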